**4.2 Study completion**

The study is considered to be finished when the last visit of the last subject in the trial is completed.

**4.3 Study termination**

The sponsor holds the right to close the study centre or suspend the study at any time. The study centre should be closed after the study is completed. The centre is considered closed after all required documentation and study supplies have been collected and a centre closure visit has been conducted.

Investigators can also request to suspend the study, but they must give reasonable reasons in advance.

Reasons for the sponsor or investigator to close the centre in advance may include, but are not limited to:

1. Investigator fails to comply with the requirements of the study protocol, IEC/IRB or local regulatory authorities, sponsor's operating procedures or GCP guidelines;
2. Security considerations;
3. Investigators are not recruiting enough subjects.

**5. Treatment administered to included subjects**

**5.1 Description of the treatment required to conduct the study**

All enrolled patients will receive intra-arterial administration of argatroban (0.2-0.3 mg/min), dexamethasone (0.1 mg/min) and edaravone (0.3 mg/min) for 30 to 60 minutes after successful recanalization. In addition, all patients in the intervention arm will receive standard medical care as per national stroke guidelines.

**5.2 Permitted and prohibited medical drugs and treatments in the study**

There are no specific medical treatments for this study. The treatments are based on the current guidelines.

**6. Outcome measurements**

**6.1 Primary efficacy outcome**

Proportion of mRS (0–2) at 90±7 days after randomization.

**6.2 Secondary efficacy outcomes**

1. Proportion of mRS (0–1) at 90±7 days after randomization;
2. Occurrence of early neurological improvement (ENI) within 48±12 hours;

**6.3 Safety outcomes**

Occurrence of symptomatic intracranial haemorrhage within 48±12 hours.

Note:

- ENI is defined as more than 4-point decrease in NIHSS within 48±12 hours;
- Sympotmatic intracranial hemorrhage is defined as an increase in the NIHSS score of ≥4 points as a result of the intracranial hemorrhage according to the ECASS-3 study [11].

**6.5 Study procedure**

**
[figure not shown]
**

**6.6 Study periods**

**Screening period:** On day 0 (baseline period), it is necessary to complete enrolment screening, and collect demographic characteristics, medical history (including history of hypertension, diabetes and drug treatment history), brain imaging (computer tomography, computed tomography angiography or magnetic resonance imaging), neurological measurements (NIHSS score, mRS score), hematological examination (blood routine, blood glucose, hepatic and renal function, coagulation routine, urine routine, electrocardiogram, etc) and other information.

**Treatment period:** All enrolled patients receive intra-arterial drugs. The perioperative data including time and dose of intra-arterial drugs, LVO recanalization time, mTICI grade, etc. will be recorded and cranial CT will be performed immediately after the procedure.

**Follow-up period:** NIHSS score will be assessed at 48±12 hours, and 10 ± 2 days. Repeated brain CT will be performed at 48±12 hours. The mRS score will be assessed at 90 ± 7 days. All concomitant medications, adverse events, stroke recurrence and other vascular events of each visit will be recorded since the last visit.

All the adverse events of included subjects should be recorded and tracked until properly resolved.

All the serious adverse events of included subjects should be recorded and tracked, even if the subjects have finished the trial, until the events are resolved, or stabilization judged by the investigator.

**7. Description of safety assessment parameters**

**7.1 Evaluate clinical safety:**

Physical examinations, including neurological assessments, imaging studies, will be performed at baseline, 48 ± 12 hours, 10 ± 2 days, and 90 ± 7 days after enrolment; adverse event of each visit will be collected after baseline visit.

**Adverse events monitoring**

All information on adverse events, whether mentioned by subjects, discovered by investigators, or discovered through physical examination, laboratory tests, and other methods, should be recorded on the adverse events page of electronical case report form and handled in accordance with appropriate regulations and report.

**Adverse Event (AE）**

The adverse event (AE) is any adverse medical event that occurs in a study subject during the course of a study that is not necessarily related to this treatment. Thus, the adverse event (AE) can be any unfavourable and unexpected sign (including abnormal laboratory findings), symptom or disease temporally related to the use of study treatments, regardless of whether it is related to the study treatments or not.

It is included that any events that are new or that have worsened in severity and frequency from baseline, including abnormal results from diagnostic methods such as laboratory tests.

Note: Adverse event collection begins with signed informed consent.

**Serious Adverse Event (SAE）**

Serious adverse event (SAE) is any adverse medical event at any dose that meets one or more of the following criteria:

• cause death (note: death is a consequence, not an event);

• Life-threatening (Note: "Life-threatening" means that the subject is in immediate danger of death at the time of the event, not the assumption that death would have occurred if the event is more severe);

• Cause significant or permanent disability or impairment of organ function;

• Teratogenic and birth defects;

• Causing or prolonging hospitalization;

• Significant medical event or need for intervention (occur without treatment)’

Note: Any event requiring hospitalization (or prolonged hospitalization) that occurs during the course of the subject's participation in the study must be reported as a serious adverse event. The following circumstances leading to hospitalization are not considered serious adverse events:

• Hospitalization for social reasons other than adverse events

• Hospitalization for a scheduled surgery or other treatment or examination prior to study entry (must be recorded on the case report form)

• Hospitalization for elective surgery or treatment or examination due to anticipated disease progression

**7.2 Safety assessment**

For all adverse events in clinical studies, the following factors must be evaluated for safety:

• Severity criteria for SAE

• The causal relationship between the event and the investigational drugs

• Severity of incident

• Anticipation of events

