| **Treatment Regimens** | All enrolled patients will receive intra-arterial administration of argatroban (0.2-0.3 mg/min), dexamethasone (0.1 mg/min) and edaravone (0.3 mg/min) for 30 to 60 minutes after the end of thrombectomy. |
| **Procedure** | **Screening period:** On day 0 (baseline period), it is necessary to complete enrolment screening, and collect demographic characteristics, medical history (including history of hypertension, diabetes and drug treatment history), brain imaging (computer tomography, computed tomography angiography or magnetic resonance imaging), neurological measurements (NIHSS score, mRS score), haematological examination (blood routine, blood glucose, hepatic and renal function, coagulation routine, urine routine, electrocardiogram, etc) and other information.  **Treatment period:** Intra-arterial administration of argatroban (0.2-0.3 mg/min), dexamethasone (0.1 mg/min) and edaravone (0.3 mg/min) for 30 to 60 minutes after the end of thrombectomy.  **Follow-up period:** NIHSS score will be assessed at 48±12 hours, and 10 ± 2 days after enrolment. At 48±12 hours, patients will receive brain computer tomography or magnetic resonance imaging. The mRS score will be assessed at 90 ± 7 days. All concomitant medications, adverse events, stroke recurrence and other vascular events of each visit are recorded since the last visit.  All the adverse events of included subjects should be recorded and tracked until properly resolved.  All the serious adverse events of included subjects should be recorded and tracked, even if the subjects have finished the trial, until the events are resolved, or stabilization judged by the investigator. |
| **Planed Duration** | 24 months |

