**Causal relationship between events and the study treatments**

Regardless of serious adverse events or non-serious adverse events, the investigator must evaluate the relevance of the event to the use of the study drugs according to the following criteria:

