**Evaluating association between adverse events and study treatments Criteria**

| **5-level classification** | **Judgment criteria** |
| --- | --- |
| Definitely related | The time of initiation of use is reasonably related to the time of occurrence of the adverse event; the adverse event corresponds to the known adverse reaction type of the study drugs; the occurrence of the adverse event cannot be explained by factors other than the study drugs; the adverse event reduce or disappear after study drug dose reduction or discontinuation; similar adverse events (non-essential) can occur with re-use of study drug. |
| Probably related | The time of initiation of use is reasonably related to the time of occurrence of the adverse event; the adverse event corresponds to the known adverse reaction type of the study drug; the occurrence of the adverse event can or cannot be explained by factors other than the study drug; the adverse event can or cannot reduce or disappear after study drug dose reduction or discontinuation; it is not sure whether similar adverse events (non-essential) can occur with re-use of study drug. |
| Probably unrelated | The time of initiation of use is not reasonably related to the time of occurrence of the adverse event; the adverse event corresponds to the known adverse reaction type of the study drug; the occurrence of the adverse event can or cannot be explained by factors other than the study drug; the adverse event can or cannot reduce or disappear after study drug dose reduction or discontinuation; it is not sure whether similar adverse events (non-essential) can occur with re-use of study drug. |
| Definitely unrelated | The time of initiation of use is not reasonably related to the time of occurrence of the adverse event; the adverse event corresponds to the known adverse reaction type of the study drug; the occurrence of the adverse event can or cannot be explained by factors other than the study drug; the adverse event can or cannot reduce or disappear after study drug dose reduction or discontinuation; similar adverse events (non-essential) cannot occur with re-use of study drug. |
| Unjudged | The judgment cannot be made due to incomplete, contradictory information or the fact that the information cannot be supplemented and verified. |

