**Table of Correlation Evaluation Criteria for Adverse Events and Drug Use**

|  | Definitely related | Probably related | Probably unrelated | Definitely unrelated | Unjudged |
| --- | --- | --- | --- | --- | --- |
| Have a reasonable chronological order with the study drug | ＋ | ＋ | ＋ | － | ? |
| For the known reaction type of the study drug | ＋ | ＋ | － | － | ? |
| Explanation for reasons other than available research equipment | － | ± | ± | ＋ | ？ |
| Responses lessen after decompression of study drug | ＋ | ± | ± | － | ? |
| The reaction reappears after the study drug is reused | + or ? | ? | ? | － | ? |

Note: "+" in the table is affirmative; "-" is negative; "±" is difficult to affirm or deny; "?" indicates that the situation is unknown.

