**7.3 Safety report**

**All adverse events**

All adverse events, regardless of their severity, nature of severity, or their causal relationship to study drug, from the time of signed informed consent until the last follow-up visit (90 days after randomization), are to be recorded in medical terms on the clinical research form. When symptoms and signs are caused by common causes, a diagnosis of the disease should be given where possible (e.g., cough, runny nose, sneezing, sore throat, and headache should be reported as "upper respiratory tract infection"). The investigator must make a judgment on the causal relationship between the adverse event and the study drug and record it on the clinical research form. All drugs for adverse events should be documented in the original medical record and reported as requested by the sponsor.

All serious adverse events in clinical research must be reported to the ethics committee of the centre, the principal investigator of the centre, the sponsor, the contract research organization, the research team leader unit, and the adverse reaction monitoring centre within 24 hours; Report to the ethics committee and data and safety monitoring committee of the team leader unit within 7 natural days after being informed. Investigators must complete a serious adverse event form to record the time, severity, duration, actions taken and outcomes of serious adverse events. Any follow-up information for serious adverse events should also be reported in writing within 24 hours according to the above process.

All serious adverse events that do not resolve at study termination or subject early withdrawal must be followed up to any of the following:

- 1. Incident mitigation
  2. Events are stable
  3. If the baseline value is known, the event returns to the baseline value
  4. Events can be attributed to other treatments or factors not related to study
  5. It is unlikely that any further information will be available (subject or physician refuses to provide further information and remains lost to follow-up after various follow-up attempts)

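### Adverse-event causality is graded against the study drugs only, so a harm caused by the intra-arterial delivery cannot be attributed to the intervention

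*Protocol*

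**What the plan says.** The intervention is argatroban, dexamethasone and edaravone given into the artery. The Protocol Abstract (Treatment Regimens) has this running "for 30 to 60 minutes after the end of thrombectomy". Section 5.1 gives the same duration: "dexamethasone (0.1 mg/min) and edaravone (0.3 mg/min) for 30 to 60 minutes after successful recanalization".

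Section 7.2 lists what must be judged for each adverse event, including "The causal relationship between the event and the investigational drugs". The subsection headed "Causal relationship between events and the study treatments" uses the wider term, but its instruction returns to the drugs: "the investigator must evaluate the relevance of the event to the use of the study drugs according to the following criteria". The written criteria that follow refer to the drugs throughout. For *Definitely related*, for example, they require that "the occurrence of the adverse event cannot be explained by factors other than the study drugs". Section 7.3 repeats the restriction: "The investigator must make a judgment on the causal relationship between the adverse event and the study drug".

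The correlation table at the end of this material also refers to the study drug, except in one row, which is labelled "Explanation for reasons other than available research equipment". The protocol defines no research equipment. The definition of an adverse event in section 7.1 also speaks of study treatments, but no passage says that the term covers the infusion procedure.

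**The concern.** An infusion that starts after thrombectomy has ended can reasonably be taken to add arterial catheter time. The protocol does not say so, but it follows from the route and the timing. Any harm from that added time is a harm of the intervention even if none of the three drugs caused it.

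Section 2.1 makes the safety of intra-arterial cocktail therapy the hypothesis, and the route is part of that therapy. The only named safety outcome (section 6.3) is symptomatic intracranial haemorrhage. Dissection, vasospasm or embolism would therefore reach the record only as adverse events, and their attribution rests on the 7.2 grading. The design is single-arm (section 3.1), so no concurrent randomised group would show an excess of such events. Event-level attribution therefore carries more weight than it would in a controlled trial.

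**Working it through.** The protocol gives no figure to reproduce here, so the check is a reading of the two grading tools in 7.2 against test events.

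**Test event A:** a dissection or vasospasm during the infusion. Assumptions: the timing is plausible, it is not a known reaction to any of the three drugs, and the catheter explains it.

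*Written criteria in 7.2*

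| Grade | Timing required | Known drug reaction required | Event A |
|---|---|---|---|
| Definitely related | plausible | yes | fails on reaction type, and on the exclusion of other explanations |
| Probably related | plausible | yes | fails on reaction type |
| Probably unrelated | not plausible | yes | fails on timing and on reaction type |
| Definitely unrelated | not plausible | yes | fails on timing and on reaction type |
| Unjudged | – | – | reserved for incomplete, contradictory or unverifiable information, so it does not apply |

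Event A has no grade.

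*Correlation table in 7.2*

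| Row | Def. related | Prob. related | Prob. unrelated | Def. unrelated | Event A |
|---|---|---|---|---|---|
| Plausible timing | + | + | + | − | + |
| Known drug reaction | + | + | − | − | − |
| Other explanation | − | ± | ± | + | + (or −, if the catheter counts as research equipment) |
| Lessens on withdrawal | + | ± | ± | − | not informative (±) |
| Recurs on re-use | + or ? | ? | ? | − | unknown (no repeat infusion is described) |

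The reaction-type row closes both related columns, however the research-equipment row is read. *Definitely unrelated* is contradicted on timing. *Probably unrelated* is the closest column, although its ± on other explanations is not an exact match.

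**Test event B:** an access-site bleed during the infusion. If bleeding counts as a known reaction to argatroban (an assumption, since the protocol lists no known reactions), timing and reaction type are both met. *Probably related* tolerates another explanation in both tools, so B can be graded *Probably related*.

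**Where the grade is used**

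- Section 7.3 has every adverse event recorded whatever its causality.
- The safety outcome in section 6.3 is not filtered by causality.
- The suspension criterion in section 3.2 turns on the proportion of serious adverse events, not of related ones.
- The analyses in section 8.2 do not use the grade.
- Section 7.3 lists attribution to other treatments or to factors outside the study as one way in which follow-up of an unresolved serious event may end. Attribution has a procedural consequence here.

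**The case against.** The strongest reply is that this is a matter of wording. The headings and the adverse-event definition say study treatments. The use of these drugs is intra-arterial by design, so an investigator could read delivery into the question. A single causality question is common and is not in itself an error. The odd row label in the table may be a translation slip. Investigators would also often be unable to separate a harm of the infusion from a harm of the thrombectomy just completed through the same kind of access.

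Part of this stands. Separating the two sources will be hard, and the row label alone does not prove that the two tools judge different objects. But the generous reading does not survive the criteria, because the requirement of a known drug reaction shuts event A out of both related grades however broadly the heading is read.

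A reader might infer three stronger things that the protocol does not support:

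- **Delivery harms are pushed into both unrelated grades.** The written criteria place event A in neither, the table points only to *Probably unrelated*, and event B can be graded as related.
- **A related-event summary is biased towards safety.** The protocol defines no such summary.
- **An assumed complication rate, such as a few per cent across 30 patients, sizes the problem.** Such a rate would not isolate the excess due to added catheter time in patients who have all just had a thrombectomy, and the protocol gives no rate.

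On serious events, the Abstract and section 6.6 also ask for tracking until resolution or stabilisation. This limits the practical reach of the 7.3 provision but leaves it in the text.

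**Conclusion.** The concern holds as a defect of attribution. As written, a delivery harm with plausible timing that is not a known drug reaction cannot be attributed to the intervention: it has no grade in the written criteria and lands nearest *Probably unrelated* in the table. Harms that resemble a known drug reaction are less affected.

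The consequence is confined to the causality record and to the 7.3 follow-up provision that depends on it. Event capture, the haemorrhage outcome and the suspension criterion are untouched, and no stated analysis changes. The conclusion assumes that the infusion adds catheter time and that events such as dissection or vasospasm are not known reactions to the three drugs. No numerical size can be given from the document. The change is worth making because safety is the hypothesis, there is no randomised control and the cost is low.

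**What to change.** 1. In 7.2 and 7.3, define the object of the causality assessment as the study intervention, meaning the drugs and their intra-arterial administration. Carry this into every criterion, including the known-reaction criterion, which is the one that now closes the related grades.
2. Add one field to the adverse-event form for relatedness to the intra-arterial delivery, meaning the period after thrombectomy has ended, beside the existing question on the drugs. Count an event as intervention-related if either answer is related.
3. Correct the research-equipment row of the correlation table so that it names the same object as the other rows.
4. Reconcile the written criteria with the table on timing and reaction type for the two unrelated grades. Otherwise event A would still have no grade on the drug question. This step alone would not be enough, because delivery would still not be assessed.

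The cost is wording in two sections and one form field, with no change to treatment, visits or sample size. Investigators will sometimes find it hard to tell delivery harm from thrombectomy harm, and the number of events graded as related may be higher.

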**Causal relationship between events and the study treatments**

Regardless of serious adverse events or non-serious adverse events, the investigator must evaluate the relevance of the event to the use of the study drugs according to the following criteria:

**Evaluating association between adverse events and study treatments Criteria**

| **5-level classification** | **Judgment criteria** |
| --- | --- |
| Definitely related | The time of initiation of use is reasonably related to the time of occurrence of the adverse event; the adverse event corresponds to the known adverse reaction type of the study drugs; the occurrence of the adverse event cannot be explained by factors other than the study drugs; the adverse event reduce or disappear after study drug dose reduction or discontinuation; similar adverse events (non-essential) can occur with re-use of study drug. |
| Probably related | The time of initiation of use is reasonably related to the time of occurrence of the adverse event; the adverse event corresponds to the known adverse reaction type of the study drug; the occurrence of the adverse event can or cannot be explained by factors other than the study drug; the adverse event can or cannot reduce or disappear after study drug dose reduction or discontinuation; it is not sure whether similar adverse events (non-essential) can occur with re-use of study drug. |
| Probably unrelated | The time of initiation of use is not reasonably related to the time of occurrence of the adverse event; the adverse event corresponds to the known adverse reaction type of the study drug; the occurrence of the adverse event can or cannot be explained by factors other than the study drug; the adverse event can or cannot reduce or disappear after study drug dose reduction or discontinuation; it is not sure whether similar adverse events (non-essential) can occur with re-use of study drug. |
| Definitely unrelated | The time of initiation of use is not reasonably related to the time of occurrence of the adverse event; the adverse event corresponds to the known adverse reaction type of the study drug; the occurrence of the adverse event can or cannot be explained by factors other than the study drug; the adverse event can or cannot reduce or disappear after study drug dose reduction or discontinuation; similar adverse events (non-essential) cannot occur with re-use of study drug. |
| Unjudged | The judgment cannot be made due to incomplete, contradictory information or the fact that the information cannot be supplemented and verified. |

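### The protocol's two causality tables define the 'unrelated' grades inconsistently, and neither lets a well-timed event of a new type be graded related

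*Protocol*

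**What the plan says.** Protocol section 7.2, under the heading on the causal relationship between events and study treatments, requires a causality judgement for serious and non-serious events alike. Two tables follow, and no rule says which prevails.

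The first (criteria for evaluating association, in prose) describes 'Probably unrelated' and 'Definitely unrelated' with the same opening: "time of initiation of use is not reasonably related to the time of occurrence of the adverse event; the adverse event corresponds" to a known reaction type. For 'Definitely related' it asks that "the occurrence of the adverse event cannot be explained by factors other than the study drugs" and that "the adverse event reduce or disappear after study drug dose reduction or discontinuation; similar adverse events (non-essential) can occur with re-use of study drug". Only the re-use item is marked non-essential.

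The second (correlation evaluation criteria, in symbols) has five rows. The row "Have a reasonable chronological order with the study drug" is positive for both related grades and for 'Probably unrelated', and negative for 'Definitely unrelated'. The row "For the known reaction type of the study drug" is positive for the two related grades and negative for the two unrelated ones. The row "Responses lessen after decompression of study drug" is positive for 'Definitely related' and negative for 'Definitely unrelated'.

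Section 5.1 describes the study treatment as an intra-arterial infusion lasting 30 to 60 minutes.

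**The concern.** An investigator following the prose table and one following the symbol table can both comply with the protocol and still handle the same event differently: one finds a grade for it, the other finds none. The conflict lies in the grades that declare an event unrelated, where an error is least likely to be looked at again.

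The handling of new reaction types matters most. The trial is a pilot of a three-drug intra-arterial combination, and safety is part of its stated objective. A harm not yet on any list is what such a pilot should be able to flag, yet neither table lets a well-timed event of that kind be called related.

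A lesser issue is that 'Definitely related' depends on what happens when the drug is reduced or stopped. That says little about an event that appears after a short infusion has already ended.

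**Working it through.** There is no sample-size or power figure to reproduce; the check compares the two tables item by item.

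**Coding.** + means the item must be present, − that it must be absent, ± that it may go either way, ? that it is unknown. The prose 'can or cannot' is coded ±, and 'not sure' is coded ?. The symbol row "Explanation for reasons other than available research equipment" is taken as the same item as the prose clause on factors other than the study drugs, and the row "Responses lessen after decompression of study drug" as the same item as lessening after reduction or stopping.

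| Grade | Table | Timing plausible | Known type | Other explanation | Lessens | Recurs on re-use |
|---|---|---|---|---|---|---|
| Definitely related | prose | + | + | − | + | + (non-essential) |
| Definitely related | symbols | + | + | − | + | + or ? |
| Probably related | prose | + | + | ± | ± | ? |
| Probably related | symbols | + | + | ± | ± | ? |
| Probably unrelated | prose | **−** | **+** | ± | ± | ? |
| Probably unrelated | symbols | **+** | **−** | ± | ± | ? |
| Definitely unrelated | prose | − | **+** | **±** | **±** | − |
| Definitely unrelated | symbols | − | **−** | **+** | **−** | − |

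**Cell count.** 4 grades × 5 items = 20 cells. The related grades agree in all 10. The unrelated grades differ in 2 + 3 = 5 of their 10 cells. Three are direct opposites: timing and known type for 'Probably unrelated', and known type for 'Definitely unrelated'. The other two ('Definitely unrelated': other explanation and lessening) differ in strictness, since the symbol value lies within what the prose allows.

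**Classifying events.** Let timing, known type and other explanation each be yes or no, lessening be yes, no or unknown, and re-use be unknown because only one infusion is described. That gives 2 × 2 × 2 × 3 = 24 profiles, 6 for each combination of timing and type.

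| Timing | Type | Prose table | Symbol table |
|---|---|---|---|
| plausible | known | Probably related in 6 of 6; 1 of these also fits Definitely related | the same |
| plausible | new | no grade in 6 of 6 | Probably unrelated in 6 of 6 |
| implausible | known | Probably unrelated in 6 of 6 | no grade in 6 of 6 |
| implausible | new | no grade in 6 of 6 | no grade in 6 of 6 |

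So 6 + 6 = 12 of 24 profiles are handled differently, each time because one table supplies a grade and the other does not. A new type never fits the prose table because all four of its grades require a known type. The 'Unjudged' class does not fill the gap: it is meant for incomplete, contradictory or unverifiable information.

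**Lessening.** The single profile that reaches 'Definitely related' is well timed, of known type, without another explanation, and lessening. If lessening is absent or unknown, the event falls to 'Probably related' in both tables.

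**Re-use.** In the prose table the two unrelated grades differ only in the re-use clause. That clause is non-essential and no re-use is described, so in practice the two grades cannot be told apart.

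**The case against.** The strongest counter-argument is that little depends on the grade. Symptomatic intracranial haemorrhage is counted by occurrence (section 6.3). All adverse events are recorded whatever their cause, and all serious ones are reported within 24 hours (section 7.3). Deaths are serious events whether or not treatment-related (section 7.3, Death). The suspension criterion in section 3.2 refers to the proportion of serious events, not of related ones. All of this stands, and it limits the point to the causality label.

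It is also fair that two of the five differing cells are differences of strictness rather than contradictions. The count above separates them.

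Three stronger readings are tempting, and the protocol does not support them.

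- A reader might infer that haemorrhage can never be 'Definitely related'. The lessening item is uninformative rather than impossible to meet. The severity and laboratory provisions in sections 7.2 and 7.3 contemplate stopping treatment, an infusion can end early, and later regression after its end could be read as lessening. A separate obstacle, the absence of any other explanation, is hard to satisfy after stroke and thrombectomy and would remain whatever is done about lessening.
- A reader might infer that haemorrhage is systematically graded down. If it counts as a known reaction type, a well-timed haemorrhage is at least 'Probably related' in both tables. The protocol lists no known types, so this remains conditional.
- A reader might infer that new harms default to 'Probably unrelated'. That holds only in the symbol table and only with plausible timing; in the prose table they have no grade.

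**Conclusion.** The point holds as an internal inconsistency in a mandatory rule. Five of 20 cells differ, three as direct opposites, all within the two unrelated grades. Half of the 24 profiles are graded by one table and left without a grade by the other. That is a count of possible combinations, not an estimate of how many events would be affected. In none of the 24 do the tables assign two different grades, so a reader should not infer that events switch between related and unrelated according to the table used.

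The most consequential result is that a well-timed event of unknown type cannot be graded related under either table. Making lessening a condition of 'Definitely related' is a lesser misfit with a short single infusion.

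The conclusion assumes that the two tables address the same five items, that 'can or cannot' means the same as ±, and that re-use is unknown. The correction is worth making because the trial's objective includes safety. It does not call the safety outcome or the reporting of serious events into question.

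**What to change.** Replace the two tables in section 7.2 with one set of criteria, or align them cell by cell, so that each grade has a single definition. In doing so:

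- ensure that a well-timed event is neither graded unrelated nor left ungraded merely because its type is not already known;
- allow the lessening and re-use items to be marked 'not applicable' for this single infusion, and say how the grade is then reached;
- since re-use is the only item separating the two unrelated grades in the prose table, separate them by something else once it can be 'not applicable';
- use the same terms for the same items, so that the rows naming research equipment and decompression refer clearly to the study drugs.

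The cost is a wording change in the protocol and the serious adverse event form, plus brief retraining. No outcome, visit or data item changes.
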